## Abstract

**Background:**

Caregivers of children undergoing growth hormone treatment often face stress and stigma. In this regard, family-centered approaches are increasingly considered, wherein caregivers’ mental wellbeing is taken into account to optimize children’s health-related outcomes and behaviors (e.g., treatment adherence). Here, mindfulness and parenting-based programs have been developed to support the mental wellbeing of caregivers and, in turn, promote richer interactions with the children. Nevertheless, this type of program can face drawbacks, such as the scheduling and availability of family members. Recent digital health (DH) solutions (e.g., mobile apps) are showing promising advantages as self-management support tools for improving wellbeing and behaviors related to the treatments. Although, further evidence is necessary in the field of Growth Hormone Treatment (GHt). Accordingly, this study aims to examine the usability of a mobile DH solution and the feasibility of a DH intervention designed to promote emotional and mental wellbeing of caregivers of children undergoing GHt.

**Methods:**

This is a prospective mixed-methods (qualitative-quantitative) exploratory study composed of two sub-studies, including caregivers of children undergoing GHt. Sub-study one (SS1; n = 10) focuses on the usability of the DH solution (detecting potential barriers and facilitators) and an ad hoc semi-structured interview will be administered to the caregivers after using the DH solution for one month. Sub-study two (SS2; n = 55) aims to evaluate the feasibility of the DH intervention on caregivers’ perceived distress, positive affectivity, mental wellbeing, self-efficacy, together with the children’s quality of life and treatment adherence. All these parameters will be assessed via quantitative methods before and after 3-months of the DH intervention. Usability and engagement will also be assessed during and at the end of the study.

**Results:**

It is expected that significant amounts of data will be captured with regards of the feasibility of the DH solution.

**Discussion:**

The manuscript provides a complete protocol for a study that will include qualitative and quantitative information about, on one hand, the user-friendliness of the DH solution, and on the other, the effects on caregivers’ emotional, as well as, behavioral parameters in terms of the usability and engagement to the DH solution. The findings will contribute to the evidence planning process for the future adoption of digital health solutions for caregiver support and better health-related outcomes.

*Trial registration* ClinicalTrials.gov, ID: NCT04812665.

**Supplementary Information:**

The online version contains supplementary material available at 10.1186/s12911-022-01935-1.

## Background

Growth hormone is prescribed in children for a range of health conditions related to growth problems and short stature, and in particular patients with growth hormone deficiency compared with peers of the same age and sex [1, 2]. Furthermore, short stature in children has also been reported to be associated with psychosocial stress, social isolation, bullying, and impaired social competencies [3–5]. This problem extends to caregivers (usually parents), that have to deal with various stressors about child’s health, such as daily stressors (managing daily routine as ensuring treatment adherence) and emotional stressors (e.g., anxiety, worrying) [6, 7] and as well as social stigma [8, 9], ultimately caregivers can be affected by emotional fatigue and burnt out.Therefore, caregivers are at risk for developing psychosocial problems, such as anxiety and depression, which can reasonably lead to greater difficulties in handling effectively the child's illness and development. A child’ mental health development depends on their parents or caregivers who serve as primary sources of support in reaching an adaptive development. Studies on the importance of parents’ mental wellbeing in the child development have showed that a poorer parents’ mental wellbeing is related to a higher mental, emotional or development disability [10]. In particular, parental stress has been associated with less effective parenting [11] and poorer adherence of children to medical treatment [12]. On contrary, positive affect states have been found to be associated with health-related quality of life (HrQoL) in adolescents with Type I diabetes [13]. In a similar vein, self-efficacy as perceived control and capability to implement a course of action [14] and mental wellbeing have also been found positively related to pediatric health outcomes [15]. However, these factors has been extensively investigated within pediatric areas such as Type-I diabetes, cancer [16], and chronic pain [17], other pediatric areas such as growth conditions are misrepresented.

These are leading to serious consideration of family-centered approaches targeting the mental wellbeing of caregivers as a pivotal factor to optimize children’s health outcomes, such as treatment adherence [18–20]. Accordingly, cognitive behavioral therapy (CBT) and mindfulness-based cognitive therapy (MBCT) have demonstrated positive outcomes regarding stress and healthy quality of life of caregivers and children [21]. On one side, CBT includes the awareness of useless and negative thoughts and related-behaviours, reframing them with positive and useful thoughts and behaviours. On the other hand, MBCT aims to support patients to pay attention to their thoughts without judgment, accepting them and reducing the impact of negative and useless thoughts and behaviours, thus, providing tools to cope with the stressful situations [22, 23]. In this theoretical context, psychoeducational modules, as well as activities such as mindfulness, have been used, showing a decrease of stress and an increase in mental wellbeing. According to the previous evidence, mindfulness activities specifically designed to improve parents' self-efficacy and stress management have been shown to promote richer interactions with the children [21, 24]. In a similar vein, standardized parenting programs have been developed to promote positive parenting skills (e.g., problem-solving and communication techniques) [25].

However, despite these positive results, parents often experience practical barriers for participation in this type of interventions, such as travelling distance, and timing costs, looking for resources to take care of the children (e.g., babysitters), and absence from work [26, 27].

To overcome these issues, digital health (DH) solutions are enabling more accessible self-management supports and less costly family-centered intervention modalities [28–30]. A few recent pilot and feasibility studies are showing positive outcomes on the efficacy of caregiver interventions of children with chronic conditions, such as diabetes, and pediatric transplants through mobile apps [28, 29]. Similarly, other studies using web applications are showing that DH interventions are feasible to deliver training programs targeting, among others, parenting stress, problem-solving skills, protective parenting behavior, or self-efficacy of caregivers of children with chronic conditions (e.g., cancer, or obesity; see the review [31]). Interestingly, to our knowledge, none of the studies delivered a mobile-based DH intervention, via smartphone for caregivers of children undergoing GHt. Starting from these premises, the aim of this study is to investigate the usability of the mobile DH solution, called Adhera® Caring, and the trial design and feasibility of Adhera Caring intervention evidence-based on CBT and MBCT for caregivers’ mental wellbeing. Accordingly, the study protocol targets to obtain qualitative and quantitative answers to the following three research questions and derived hypotheses:What is the overall usability experience of caregivers using Adhera Caring?Hypothesis 1: Participants will show an acceptable usability experience of the DH solution.What effect does the intervention through Adhera Caring have on the levels of psychological distress, mental well-being, self-efficacy, of caregivers of children undergoing GHt for short stature?Hypothesis 2: The intervention will improve the levels of psychological distress, and will promote positive affect, self-efficacy, and mental wellbeing.Which insights can be obtained regarding parental concerns, the children’s quality of life, and adherence to treatment?

Hypothesis 3: It can be expected that promoting levels of positive affect, self-efficacy, and mental wellbeing will be positively associated with children’s quality of life and treatment adherence.

### The Adhera® Caring digital health intervention

Own prior research has built upon mental health and technology acceptance theoretical frameworks [32] to test behavioral change and mental health support via digital techniques within health-related areas such as smoking cessation [33]. We developed a digital solution incorporating three main components. An educational health content component provides general health information about a particular condition and information on self-care and stress management. The solution also incorporates a mental-wellbeing module, which also includes psychoeducational information and different actionable activities such as attention exercises based on mindfulness. Finally, a recommender system, based on artificial intelligence (AI), which delivers short messages in the form of quick actionable suggestions or educational reinforcement.

Building upon this structure, the Adhera Caring is a DH intervention mobile-app-based that has been specifically designed to support caregivers of children undergoing a GHt for short stature with regards of reducing psychological distress and improving their overall mental wellbeing, positive affect, and self-efficacy. Accordingly, the Adhera Caring DH intervention program includes: a) a psychoeducational module; b) a mental wellbeing module to reduce psychological distress and to promote positive affect and mental wellbeing; c) a behavioral change module aiming at providing brief psychoeducational messages, promoting healthier lifestyles and self-efficacy.

### Adhera Caring: psychoeducational modules

The psychoeducational modules have been designed to provide specific educational contents on childhood growth disorder and the related GHt, as well as benefits and secondary effects of the GHt, and problem-solving suggestions on how to support the children during the entire GHt process. This content includes 39 units divided into four sections) managing growth hormone deficiency; b) habits that improve life with growth hormone deficiency; c) adjusting to living with a growth hormone deficiency; d) taking care of yourself to be able to take care of your child (Fig. 1). The read contents will be marked with a tag and a progress bar appear according to the read contents. At the end of each module, the last unit consists of a quiz with multiple choices. After each answer, an explanation will be provided to the user (Fig. 2). All the material contents have been setup according to the Patient Education Materials Assessment Tool (PEMAT) guide on the understandability and actionability materials.

**Fig. 1 Fig1:**
[figure not shown]
Adhera Caring: psychoeducational modules

**Fig. 2 Fig2:**
[figure not shown]
Adhera Caring: The quiz unit (gamification element) with the explanation of the answer

### Adhera Caring: the behavioral change module

The behavioral change module reinforces the psychoeducational module by delivering brief educational messages on the childhood growth disorder, as well as support in managing psychological distress, improving self-efficacy (caregiver perception of their ability to manage child-related stressful situations e.g., facing fear to the treatment), personal skills for self-regulation (in stressed and anxiety events). It also provides lifestyles suggestions and action planning (actions to perform the desired behaviors and coping or maintaining planning) that will be sent to the patient with a set frequency (one daily; Fig. 3). The messages have been defined and validated by clinicians and behavioral change experts. When a message will be sent by this module, patients can then read them from an inbox of messages in their Adhera Caring app. The sent messages will be selected by the artificial intelligence of the Adhera Precision Digital Companion™ Platform to maximize the interest of the message for each patient—so each patient will receive tailored messages. Each message can then be rated between 1 and 5 stars, as feedback for the system to learn about the patients' preferences and improve their future recommendations.

**Fig. 3 Fig3:**
[figure not shown]
Adhera Caring: Motivational messages and ratings

#### Adhera Caring: mental well-being module

The mental wellbeing module provides patients with evidence-based CBT and MBCT-based activities to improve their mental wellbeing. They include visually guided activities to perform using the phone, audios where a psychologist instructs the patient how to relax, and audio files with relaxing music. In addition, other mental-wellbeing activities are also explained to be done without the need of using the smartphone. Pre- and post- each activity, user will rate on a 1–5-Likert scale mental wellbeing emotional states. A final report on the before and post mental wellbeing rates will be showed to the user (Fig. 4).

**Fig. 4 Fig4:**
[figure not shown]
Mental Wellbeing activities and emotional pre-and post-evaluation

#### Digital health ecosystem for treatment adherence

The recruitment for Adhera Caring Digital Health Intervention relies on the existing digital health ecosystem around the growth hormone treatment with recombinant human GH (r-hGH, somatropin, Saizen®, the healthcare business of Merck KGaA, Darmstadt, Germany) [34], that includes the use of an automated electronic injection device called Easypod™, that can be used voluntarily by the patient (and/or caregiver) to administer the growth hormone therapy [35]. The device transmits the data (time, date and dose) to a secure web-based portal called Easypod Connect where clinicians can monitor and manage herence levels of patients. This platform will be used to screen potential participants in the study with sub-optimal levels of adherence, and will be used to capture information on the impact of the intervention in adherence.

The solution Adhera Caring is part of the Adhera® Health  Precision Digital Companion™ Platform, which has been developed using the best practices with regards of data protection and quality management in accordance with the guidelines of the ISO 27001 and ISO 13465.

## Methods

### Design and setting

This is a prospective mixed-methods usability and feasibility study intervention, see Additional File 1 for SPIRIT diagram. The study will be composed of two single group sub-studies (SS1 and SS2) targeting caregivers of children undergoing GHt in accordance with general clinical practice in Spain and the Miguel Servet Children’s University Hospital (Zaragoza, Spain) where patients are already supervised by a pediatric endocrinologist.

The goal of sub-study 1 (SS1; n = 10) is to gain qualitative insights about psychological burdens experienced by caregivers of children undergoing GHt, and barriers/facilitators after using the DH solution for one month. Insights from SS1 will serve to provide an optimized version of the mobile solution for its use in sub-study 2 (SS2; n = 55). In this case, psychological parameters in terms of psychological distress, positive affect, mental wellbeing, and self-efficacy will be targeted and assessed before and after using the DH solution (pre-post design). Children’s quality of life, treatment adherence, and system usability.

### Sample size

In qualitative research, the sample size cannot be conclusively estimated since it is determined by the saturation of the data acquired during the analysis of the qualitative data (e.g., semi-structured interviews). However, the sample size in SS1 has been estimated as n = 10, based on similar studies assessing the acceptance of a mobile solution, wherein the sample size for interviews and feasibility pilots was between 10–20 participants [36, 37]. Data saturation in the qualitative thematic analysis is expected to be achieved in less than ten subjects due to the focused nature of the study. In the case that this saturation is not achieved, the sample will be extended to include ten more participants.

In SS2, a sample size of n = 55, has been estimated by the GPower v.3.1.9.2 software. Specifically, a study design with 55 participants is appropriate to detect a low-to-medium effect size (Cohen’s *d* = 0.40) with a probability of α = 0.05 associated with a power of 1—ß = 0.08. The estimation is based on mean group differences between the baseline assessment and 3-months of follow-up (i.e., two-sided one-sample t-test).

Participants will be followed after Informed Consent Form (ICF) signature at the hospital to the end of the data collection period. It should be noted that in SS1, participants would engage with the solution for 1 month after recruitment. Since SS1 mainly focuses on usability, we estimated a period of one month, so that participants have a reasonable time to test the DH solution and subsequently rise concerns, barriers or facilitators when using the app. During this one-month observation time, participants will be supported if any doubt or concern arises.

In SS2 participants will be able to engage with the solution, for 3 months. The timing has been established on the standard mindfulness-based training programs that last a minimum of eight weeks [38]. Since the DH solution is self-administered, we added one extra month so that participants have more time to engage with the proposed activities. Major protocol amendments, if any, will be rigorously handled and updated at the ClinicalTrials.gov registry. The present study protocol has been elaborated following the recommendations for study protocols [39] based on the CONSORT extension statement for feasibility trials and the Standard Protocol Items: Recommendation for Interventional Trials (SPIRIT; see Additional file 1).

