### Recruitment

Participants will be recruited from the Pediatric Endocrinology unit at the Miguel Servet Children’s University Hospital. This public hospital provides pediatric health attention to the regional area of Zaragoza (Spain), which covers an approximate 367,110 inhabitants. Participants will be recruited at the pediatric unit by the study site investigator, which is a pediatric endocrinologist experienced in the management of children with growth disorders and their associated team. Enrollment in the study will be based on the information available in the Electronic Health Record (EHR) of potential participants. Whenever a candidate is found suitable, participation in the study will be offered during routine consultations. Participants will sign an informed consent during routine clinical visits to the center. For accessing treatment, adherence data (via Easypod-Connect) of children aged 12 years old and over, a specific ICF will need to be signed according to the Spanish regulation.

Participants will be free to discontinue the study at any time. Reasons to abandon the study will be recorded in the Electronic Case Report Form (eCRF; e.g., no perceived benefit of the mHealth solution, failure to attend the scheduled visit, etc.).

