### Data analysis plan

Qualitative data in SS1 will be gathered by means of video/audio interview recordings, which need to be transcribed and coded, first, to be able to manage a more standard dataset. Subsequently, all recordings will be deleted to preserve participants’ anonymity. At least two different reviewers conduct data analyses, independently. Through the iterative process, themes and subthemes will be identified and coded as barriers or facilitators associated with the use of the eHealth solution (Deductive part). Thematic content analysis will be performed afterwards (Inductive part) (37, 54). Descriptions of demographic, clinical, and usability data will be reported in a specific section.

Quantitative data in SS2 will be gathered in a different dataset. Descriptions of demographic and the study outcomes (frequencies, mean, standard deviation, median, maximum-minimum values data, skewness, and kurtosis) will be reported in a specific section. To analyze intervention effects on the primary outcome (i.e., Positive Affect), one sample t-test between baseline and 3-month follow-up scores will be performed. Similarly, pre-post data regarding the secondary outcomes (I.e., psychological distress, self-efficacy, mental wellbeing, and children’s quality of life) will also be examined by t-tests. Bonferroni correction will be used to account for multiple comparison testing. A non-parametric approach (I.e. Mann- Whitney *U* test) will be used in the case that the data shows departures from normality distributions.

In addition, exploratory analyses will also include correlations to identify relevant associations between demographic, primary, secondary outcomes, as well as, childrens’ QoL, treatment adherence, and usability.

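### The power printed for sub-study 2 (0.08) is wrong: the stated inputs give 0.83 with 55 caregivers, and the calculation should be rerun and its sidedness confirmed

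*Protocol article*

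**What the plan says.** The Sample size section of the protocol article gives the whole calculation for SS2 in three sentences.

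- Sample size and software: "In SS2, a sample size of n = 55, has been estimated by the GPower v.3.1.9.2 software".
- Target effect: a "low-to-medium effect size (Cohen’s *d* = 0.40").
- Error rates: "with a probability of α = 0.05 associated with a power of 1—ß = 0.08".
- Test: the comparison is between baseline and 3 months, "i.e., two-sided one-sample t-test".

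The Data analysis plan names the same test for the primary outcome of SS2, positive affect: a "one sample t-test between baseline and 3-month follow-up scores will be performed". SS2 is a single-group pre-post study, so no allocation ratio enters the calculation.

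**The concern.** Power is the probability that the primary test detects the target change if that change is real. A printed value of 0.08 says that SS2 would miss its target effect 92 times in 100. That cannot be squared with the claim, in the same sentence, that 55 participants are suitable for detecting it.

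This sentence is the article's only quantitative justification for the size of SS2, and it is what a reader would use to interpret a non-significant result on positive affect. Moving the decimal point to 0.80 may not be the whole correction. If the remaining inputs do not return 55 either, another element of the sentence, such as the sidedness, may also be misreported.

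**Working it through.** **Inputs, all from the Sample size section:** n = 55, d = 0.40, alpha = 0.05, two-sided one-sample t-test, printed power 0.08.

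**Method.** For a one-sample t-test on within-caregiver changes, the test statistic under the alternative follows a noncentral t distribution with df = n − 1 and noncentrality d × √n, where d is the mean change divided by the SD of the changes. Two-sided power is the probability that this statistic falls above t(0.975; df) or below −t(0.975; df).

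**Step 1: the plan's own figure.** With n = 55, df = 54, noncentrality = 0.40 × √55 = 2.966 and critical value = 2.005. Power = 0.830. The printed 0.08 is not reproduced.

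**Step 2: the sample size that 0.08 would need.** n = 3 gives 0.072 and n = 4 gives 0.089, so 4 caregivers would be enough.

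**Step 3: the smallest n under other readings of the power** (same d, alpha and two-sided test):

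| Power read as | Smallest n |
|---|---|
| 0.80 | 52 |
| 0.85 | 59 |
| 0.90 | 68 |
| 0.92 (0.08 taken as beta) | 73 |

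For 0.80, n = 51 gives 0.7999 and n = 52 gives 0.808. The normal approximation, ((1.960 + 0.842)/0.40)² = 49.06, gives 50. None of these is 55.

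**Step 4: routes that do arrive at or near 55.**

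| Route | n | Status in the article |
|---|---|---|
| Two-sided, 80% power, 5% loss: 52/0.95 = 54.7 | 55 | No loss allowance stated |
| One-sided, 90% power (n = 54 gives 0.896; n = 55 gives 0.9005) | 55 | Contradicts the stated two-sided test |
| Two-sided Wilcoxon signed-rank, 80% power, normal-theory efficiency 3/π | 54 (power 0.812 at 55) | The calculation names a t-test |

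**Step 5: is 55 enough?** With two-sided alpha 0.05 and 80% power, the smallest detectable standardised change at n = 55 is 0.385, which is below the target of 0.40. It is enough.

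**The case against.** The strongest reply is that this is an obvious misprint. The true power follows from n, d and alpha and is 0.83 whatever was printed. The text calls 55 suitable for detecting the effect, not the minimum that does so, so choosing 3 more than 52 is harmless. The test matches the planned primary analysis, and the study is described as exploratory. All of this stands, and it limits the point to a reporting correction. It does not remove the point: the printed figure is still false, and the article does not show how 55 arose.

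A reader might infer four stronger things that the article does not support.

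- **That SS2 is practically without power.** It is not; the design has 0.83 for the stated effect.
- **That 55 cannot be obtained at all, so the statement does not describe the trial.** Step 4 shows routes to 55, and the test in the calculation is the test in the Data analysis plan.
- **That the plan ignores drop-out.** The Recruitment section says "Participants will be free to discontinue the study at any time", but this implies no rate, and the article does not say whether 55 means enrolled or completing. A condensed article may leave a loss allowance to the full protocol. For scale only, with assumed losses of 10% (49 left) and 20% (44 left), power would be 0.78 and 0.74.
- **That calling the effect low-to-medium is wrong because it depends on the pre-post correlation.** The effect size for a one-sample t-test is the standardised change, and the article makes no claim on the raw-score scale. Naming the SD in the restatement is a clarification.

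**Conclusion.** Wrong as written. The stated power of 0.08 should read 0.83 for 55 caregivers, or the sentence should say that at least 80% is reached. This rests only on the article's own n, d, alpha and test, with all 55 contributing both assessments.

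That 0.08 was meant as 0.80 is the most plausible reading, but it is an inference. Under it 55 is adequate, with 3 more than the minimum of 52. The exact match with a one-sided test at 90% power does not show that such a test was run. It is a reason to check the sidedness, because if that was the calculation, the stated two-sided test would be a second error in the same sentence. Neither the planned sample size nor the planned primary analysis is shown to be inadequate.

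**What to change.** Rerun the calculation, confirm that it is two-sided, and replace the power statement with wording such as: *55 caregivers with both assessments give 83% power (52 give 80%) to detect a mean change of 0.40 SD of the within-caregiver differences, two-sided alpha 0.05.* Add a short clause saying how 55 was reached from 52, whether by rounding up, a loss allowance or another route. If the rerun shows that a one-sided calculation was used, state that openly and give the two-sided figure alongside it, since 0.83 is the power of the test as now described.

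The cost is a rerun in the same software and a correction to one paragraph, carried into any other study document that repeats the figure. Enrolment, visits and the primary analysis do not change.
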